#### Calculation of caloric requirements

The caloric requirement is calculated by the clinical dietitian on study day 1 and then recalculated on study day 7 ± 1 using different predictive equations [see Additional file
1, Appendix A] depending on body mass index (BMI) and whether the patient is breathing spontaneously or is mechanically ventilated
[19-22]. The Penn State Equation is used for mechanically ventilated patients with BMI <30, and the Ireton-Jones, 1992 Equation is used for mechanically ventilated patients with BMI ≥30 and for spontaneously breathing patients.

#### Calculation of protein requirement

Both study groups receive their daily protein requirements. Protein requirements are based on nutritional status, degree of stress of disease or injury and physiological capability to metabolize protein. For the metabolically stressed patient, current SCCM/ASPEN clinical practice guidelines recommend 1.2 to 1.5 g of protein/kg/day
[17,23].

#### Blood glucose management

In both groups, the target blood glucose level is 4.4 to 10 mmol/L (80 to 180 mg/dL). Study centers may use their own insulin therapy protocols to achieve this blood glucose target.

#### Other co-interventions

The use of propofol for sedation, which adds to the caloric intake, is administered according to the treating team. Each 1 ml of propofol (propofol 1% or 2% Fresenius) provides 1.1 Kcal. To reduce the caloric intake from propofol, the following are recommended: 1) minimize the use of propofol; 2) use propofol for short term sedation (up to 72 hours) as per SCCM guidelines
[17]; and 3) limit caloric intake from propofol to ≤500 kcal/day for patients who weigh >70 kg and ≤300 kcal/day for patients who weigh ≤70 kg. The use of dextrose-containing fluids is according to the treating team and the insulin protocol. However, the caloric contribution of dextrose and propofol is accounted for by adjusting the enteral nutrition caloric intake on a daily basis by the study team.

To account for the volume difference between the two groups, patients in the permissive underfeeding receive 2 mL/kg of normal saline or water every four hours (based on an estimated difference in the administered volume of 30 to 40 ml/hour between the two intervention groups) by the same enteral route unless otherwise specified by the physician. All receive multivitamins (including vitamin E, vitamin C) and trace elements (selenium, zinc and copper) on a daily basis. All other co-interventions are left to the discretion of the treating team.

#### Duration of the intervention

The allocated intervention is continued until any of the following criteria is met: 1) a maximum of 14 days on the study feeding protocol; 2) ICU discharge; 3) ICU mortality or decision to withhold feeds as a part of a palliative care plan; or 4) oral feeding started and tolerated for >24 hours.

### Data collection, frequency and duration of follow-up following recruitment

At baseline for all randomized patients, data obtained include demographics, presence of co-morbidities such as chronic health problems, medication use prior to admission, Acute Physiology and Chronic Health Evaluation Scores (APACHE) II
[24] and III
[25] and presence of sepsis upon admission. Nutritional data (total calories and total protein), laboratory data (morning blood glucose, total insulin, hypoglycemic episodes, creatinine, potassium, magnesium and phosphorous), fluid input–output and stool frequency are recorded on a daily basis until a maximum of 14 days of ICU stay, ICU discharge or ICU mortality, whichever comes first. Data about healthcare-associated infections are also collected until two days after ICU discharge.

### Outcome measures

The primary outcome is 90-day all-cause mortality. Secondary outcomes include ICU, hospital, 28-day and 180-day mortality rates and Sequential Organ Failure Assessment (SOFA) scores (on days 1, 3, 7, 14, 21 and 28). Tertiary outcomes include ICU and hospital LOS, hypoglycemia, hypokalemia, hypophosphatemia, hypomagnesemia, health care-associated infections
[26], refeeding syndrome
[27], and diarrhea
[28]. Definitions of different outcomes are outlined in Additional file
1: Appendix B. Hospital mortality is censored at one year from the date of enrollment. Vital status at day 90 and day 180 are recorded if needed by telephone interview with the patient or his/her surrogate decision maker.

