**Method/Design:**

This is an international multi-center randomized controlled trial in critically ill medical- surgical adult patients. Using a centralized allocation, 862 patients will be randomized to permissive underfeeding or target feeding. Patients in the permissive group receive 50% (acceptable range is 40% to 60%) of the calculated caloric requirement, while those in the targeted group receive 100% (acceptable range 70% to 100%) of the calculated caloric requirement. The primary outcome is 90-day all-cause mortality. Secondary outcomes include ICU and hospital mortality, 28-day, and 180-day mortality as well as health care-associated infections, organ failure, and length of stay in the ICU and hospital. The trial has 80% power to detect an 8% absolute reduction in 90-day mortality assuming a baseline risk of death of 25% at an alpha level of 0.05.

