#### Statistical and analytical plan

Patients will be analyzed according to the intention-to-treat principle, that is, all randomized patients will be analyzed in the groups to which they were originally allocated. Baseline characteristics will be summarized by carrying out univariate analyses. Categorical variables will be presented as numbers and percents, whereas the continuous variables will be presented as mean and standard deviations. The primary and secondary outcomes between the two intervention groups will be compared using the Chi-square test. The relative risk reduction, absolute risk reduction and the number needed to treat with the permissive underfeeding diet to prevent one death will be calculated. Moreover, the mechanical ventilation duration and ICU and hospital LOS in the two arms will be compared using the independent Student’s t-test. For binary outcomes, logistic multivariate regression will be used to test the intervention effect, controlling for covariates when appropriate, such as when analyzing subgroups. Adjusted relative risks and associated 95% CIs will be estimated using Cox proportional hazards regression modeling. Primary outcome will also be analyzed using survival analysis. All tests of significance will be at the 5% significance level, and two-sided. Analyses will be conducted using SAS version 9.2 and/or SPSS.

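### SOFA scores on six days fall under a chi-square rule for secondary outcomes, a test that ignores the order of the score, its day-1 value and its repetition

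*Protocol article*

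**What the plan says.** Under Outcome measures, the secondary outcomes are four mortality rates (ICU, hospital, 28-day and 180-day) and "Sequential Organ Failure Assessment (SOFA) scores (on days 1, 3, 7, 14, 21 and 28".

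Under Statistical and analytical plan, the general rule is "The primary and secondary outcomes between the two intervention groups will be compared using the Chi-square test". The same paragraph treats other data types separately:

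- A t-test is named for a short list: "mechanical ventilation duration and ICU and hospital LOS in the two arms will be compared using the independent" Student's t-test. SOFA is not on it.
- A model is named for yes/no data: "For binary outcomes, logistic multivariate regression will be used to test the intervention effect".
- Cox regression is named for adjusted relative risks, and survival analysis for the primary outcome.

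No sentence gives SOFA a method for an ordered or repeated score, and none says that it will be dichotomised or grouped.

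The tiers also differ between sections. After the mortality outcomes, the abstract's list of secondary outcomes continues "as well as health care-associated infections, organ failure, and length of stay in the ICU and hospital". The outcome section says "Tertiary outcomes include ICU and hospital LOS" and puts health care-associated infections in the same tertiary list.

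**The concern.** This is a stated choice, not an omission left to a fuller document. The article assigns a test by outcome tier, and SOFA is the one secondary outcome in the body of the article that is not a yes/no event.

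A chi-square test on SOFA treats score levels as unordered categories. A difference between 6 and 7 counts the same as one between 6 and 16. It makes no use of the day-1 score, and it handles each scheduled day as a separate table although the same patients contribute to several of them. If the score is first grouped, the cut-points decide the result, and none is fixed.

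At stake is the only outcome in the article's secondary list that measures organ failure. A real difference could be missed because of the test, and an unstated grouping could be settled after the data are seen. The differing tier lists add a smaller problem: infections and length of stay could be reported under either label.

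**Working it through.** **1. The plan's own figure.** The only sample-size figure is 431 per arm, for 90-day mortality of 25% against 17% (two-sided 0.05, power 80%). With mean proportion 0.21:

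n0 = [1.960·√(2·0.21·0.79) + 0.842·√(0.25·0.75 + 0.17·0.83)]² / 0.08² = (1.129 + 0.482)² / 0.0064 ≈ 405.7

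With continuity correction: n = (n0/4)·[1 + √(1 + 4/(n0·0.08))]² = (405.7/4)·(2.060)² ≈ 430.4, rounded up to 431. The figure is reproduced, and SOFA plays no part in it.

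**2. Which test applies to SOFA.** Secondary outcome: yes (Outcome measures). Rule for secondary outcomes: chi-square. On the t-test list: no. Binary: no, and no cut-off is given. Chi-square is therefore the only test that the text assigns.

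**3. What the choice costs on a single day.** The article gives no SOFA distribution, so every input here is assumed: integer scores from 0 to 24, roughly normal, means 7 and 6, SD 4, 300 evaluable patients per arm, two-sided 0.05.

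- t-test: 1 / (4·√(2/300)) = 3.06; power = Φ(3.06 − 1.96) = Φ(1.10) ≈ 86%.
- One split at 7 or more: the proportions are Φ(0.125) = 0.550 and Φ(−0.125) = 0.450. Then z = 0.0995 / √(2·0.25/300) = 0.0995 / 0.0408 = 2.44; power = Φ(0.48) ≈ 68%.

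Simulation on the same inputs:

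| Test | Power |
|---|---|
| Chi-square over all score levels | 34% to 36% |
| Chi-square, four categories | 68% |
| Chi-square, one split at 7 | 69% to 72% |
| Rank test | 84% to 86% |
| t-test | 86% to 87% |

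The ranges reflect variation between repeated runs.

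**4. Other assumptions.** With mean 9, SD 3 or 4, true difference 0.5 to 1.0 points and 250 to 431 per arm, power runs from 8% to 85% for chi-square over all levels, from 20% to 98% for one split at 9, and from 28% to over 99% for a rank test. An intermediate case (SD 4, difference 0.8, 431 per arm) gives 29%, 66% and 81%. The order of the three was the same in every setting tried.

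**5. Validity.** With no true difference (431 per arm), rejection rates were 3.8% (all levels), 4.8% (one split) and 5.4% (rank test). On any one day the chi-square test does not produce excess false positives. The cost is power.

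**6. Several days.** Six independent tests at 5% would give 1 − 0.95⁶ = 26.5%. That overstates the risk here, because scores within a patient are correlated and day 1 is largely a baseline value. Five tests with an assumed correlation of 0.5 to 0.7 give about 15% to 18%.

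**The case against.** **Loose drafting.** The chi-square sentence is followed directly by risk reductions and the number needed to treat to prevent one death, and all other secondary outcomes in the body are mortality rates. It was probably written with mortality in mind. That is plausible, and it makes the correction easy, but as written the rule covers SOFA and nothing else does.

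**Chi-square can be used.** This stands. A grouped or split score can be tested, and with a sensible split the loss is about 15 points, not 50. The larger loss arises only if every score level is a category, which the article does not say.

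**A stronger reading: patients who died or left the ICU are ignored.** A reader might infer this, or that most scores are missing by days 14 to 28. The article supports neither:

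- It states that "all randomized patients will be analyzed in the groups to which they were originally allocated".
- It leaves outcome definitions to an appendix that is not shown, and an article commonly leaves the handling of such scores to the full protocol or analysis plan.
- It gives no figure for ICU stay or SOFA availability.
- Certain nutritional and laboratory data "are recorded on a daily basis until a maximum of 14 days of ICU stay, ICU discharge or ICU mortality, whichever comes first", but that list does not name SOFA, so it does not contradict a SOFA schedule running to day 28.

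With planned 90-day mortality of 25%, some later scores will be cut off by death. That is a reason to choose a method with a stated rule, not evidence of an error.

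**A stronger reading: the tier mismatch changes the test for length of stay.** It does not remove the t-test, which is named for length of stay whatever its tier. A yes/no infection outcome suits chi-square in either tier. The mismatch is a labelling matter.

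**Conclusion.** The point holds in a limited form. The article assigns a chi-square test to an ordered score measured on six days, without an exception or a cut-off, and the test suits that outcome poorly. On the assumed inputs the power lost against a rank test on a single day is roughly 15 points with one split and roughly 50 points over all score levels. These figures are illustrations, because the article gives no SOFA mean, SD or expected difference. The direction does not depend on them; the size does.

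The multiplicity figure of 26.5% is an upper bound and only a supporting point. The conflict between the abstract and the outcome section over infections and length of stay is real but secondary. All of this concerns non-primary outcomes: the 90-day mortality analysis and the sample size of 862 stand as they are.

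**What to change.** 1. Limit the chi-square sentence under Statistical and analytical plan to binary outcomes.
2. Name one pre-set analysis for SOFA suited to a repeated ordered or continuous score. One example is a mixed model adjusted for day-1 SOFA and for center, since randomization is stratified by center. Other methods for ordered repeated data would also meet the point.
3. State how scores after death or ICU discharge are treated. A mixed model does not settle this by itself.
4. Use a single list of secondary and tertiary outcomes in the abstract and under Outcome measures.

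The cost is a few sentences and one corrected list, with no change to sample size or primary analysis. The one real burden is step 3: any convention for patients who die or are discharged is partly arbitrary, so it should be fixed before treatment groups are compared.

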### Administrative and ethical aspects

The study sponsor is KAIMRC. The coordinating study center is the Intensive Care Department at King Saud bin Abdulaziz University for Health Sciences (KSAUHS)/King Abdullah International Medical Research Center (KAIMRC) in Riyadh, Saudi Arabia. Participating centers include the Ottawa Hospital (General and Civic campuses), Ottawa, Canada; Mount Sinai Hospital, Toronto, Canada; and King Faisal Specialist Hospital and Research Center, Riyadh, Saudi Arabia.

The study is being conducted in accordance with the International Conference on Harmonization-Good Clinical Practice (ICH-GCP) guidelines. The study protocol and the informed consent have been approved by the KSAUHS/KAIMRC Institutional Review Board (IRB) (approval number IRBC/109/10) followed by the respective IRBs of all the participating centers.

Several measures are taken to ensure optimal compliance with the study protocols. Before launching the study, ICU physicians, nurses and dietitians attended training sessions with special emphasis on adjustment of feeding to achieve the target caloric intake. The Steering Committee ([name], [name], [name], [name], and [name]) is responsible for overall management of the study including providing central guidance to support participating centers for protocol adherence, addressing challenges with protocol implementation, formulating the analysis plan, reviewing and interpreting data and preparing the manuscript. The average caloric intake is compared between the two groups on a regular basis every two months and is stratified by center. Feedback is provided to each center to further improve adherence to caloric targets, if needed. The sponsor has appointed an independent monitor who ensures that the trial is conducted in accordance with the ethical principles of the Declaration of Helsinki and the ICH-GCP guidelines. The monitor has direct access to case report forms, the source document and the trial master file at the coordinating study center. The study also has an independent Data Monitoring Committee (DMC) which is responsible for overseeing the safety of study patients, monitoring efficacy and protocol adherence and making recommendations to continue or terminate the study based on safety analysis results. The DMC is composed of three members who are not involved in the planning or execution of the study.

### Analytical plan

#### Sample size

In our recent RCT
[15], we observed an absolute risk reduction in hospital mortality of 8% (95% CI 0.4% to 25%). Based on an estimated 90-day mortality of 25% and using a power of 80% and an alpha of 0.05, the sample required to demonstrate a decrease in mortality of 8% was 431 in each group (a total of 862 patients). The flow of patients through the study will be displayed in a ‘CONSORT’ diagram (Figure
1). 

**Figure 1 F1:**
[figure not shown]
Flow diagram.

#### Statistical and analytical plan

Patients will be analyzed according to the intention-to-treat principle, that is, all randomized patients will be analyzed in the groups to which they were originally allocated. Baseline characteristics will be summarized by carrying out univariate analyses. Categorical variables will be presented as numbers and percents, whereas the continuous variables will be presented as mean and standard deviations. The primary and secondary outcomes between the two intervention groups will be compared using the Chi-square test. The relative risk reduction, absolute risk reduction and the number needed to treat with the permissive underfeeding diet to prevent one death will be calculated. Moreover, the mechanical ventilation duration and ICU and hospital LOS in the two arms will be compared using the independent Student’s t-test. For binary outcomes, logistic multivariate regression will be used to test the intervention effect, controlling for covariates when appropriate, such as when analyzing subgroups. Adjusted relative risks and associated 95% CIs will be estimated using Cox proportional hazards regression modeling. Primary outcome will also be analyzed using survival analysis. All tests of significance will be at the 5% significance level, and two-sided. Analyses will be conducted using SAS version 9.2 and/or SPSS.

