**Discussion:**

Patient recruitment started in November 2009 and is currently active in five centers. The Data Monitoring Committee advised continuation of the trial after the first interim analysis. The study is expected to finish by November 2013.

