### Randomization

PermiT is a multicenter open-label international RCT. The patients who meet all inclusion with no exclusion criteria are randomized into one of the two intervention arms: the permissive underfeeding group or target feeding group. Randomization is based on computer-generated random permuted blocks of four and is stratified by center and follows a concealed process using sealed and numbered envelopes that allocate the patient to either of the two arms of the study.

Patients may be randomized into PermiT only once unless they were discharged from the hospital and were re-admitted beyond 180 days of the first enrollment. The study does not allow cross-overs and if any occur, they will be reported as protocol violations.

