#### Subgroup analyses

The following are *a priori* subgroups that will be analyzed: non-operative and operative patients, diabetic and non-diabetic patients, APACHE II ≤18 and >18, specific admission diagnoses (sepsis and traumatic brain injury), patients on vasopressors at baseline and those who are not and inclusion blood glucose (categorized according to the median value).

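### The only test named for comparing 90-day mortality uses neither center nor baseline APACHE II, and the adjusted analyses are left unspecified and unranked: a loss of efficiency, not an error

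*Protocol article*

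**What the plan says.** All references are to the Protocol article.

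- **Randomization:** "Randomization is based on computer-generated random permuted blocks of four and is stratified by center". The abstract's discussion paragraph adds: "Patient recruitment started in November 2009 and is currently active in five centers".
- **Data collection, frequency and duration of follow-up following recruitment:** the baseline data for all randomized patients include "Acute Physiology and Chronic Health Evaluation Scores (APACHE) II" and III. Under Subgroup analyses the same score defines an a priori split: "APACHE II ≤18 and >18".
- **Statistical and analytical plan, group comparison:** "The primary and secondary outcomes between the two intervention groups will be compared using the Chi-square test". Center is not mentioned in that section. Relative and absolute risk reductions and a number needed to treat are to accompany the comparison.
- **Statistical and analytical plan, further analyses:** "For binary outcomes, logistic multivariate regression will be used to test the intervention effect, controlling for covariates when appropriate, such as when analyzing subgroups". Then: "Adjusted relative risks and associated 95% CIs will be estimated using Cox proportional hazards regression modeling". The primary outcome is also to receive a survival analysis. No covariate is named for any model, and no order of precedence is given.
- **Sample size:** "Based on an estimated 90-day mortality of 25% and using a power of 80% and an alpha of 0.05", with 431 patients per group to show a fall of 8 percentage points.

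**The concern.** Two baseline facts are known for every randomized patient: the center, which is the only stratification factor, and a severity score that the article itself treats as important enough for a subgroup analysis. The test named for the primary outcome uses neither. When a baseline score predicts death, adjusting for it gives more power from the same patients, so the plain test gives up precision that would cost nothing to keep.

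The adjusted analyses in the same section do not settle the matter. They name no covariates, the logistic model controls for them only conditionally, and nothing says whether the chi-square, the logistic model or the Cox model answers the primary question if they differ. The promised absolute risk reduction and number needed to treat have no stated adjusted counterpart: a logistic model gives a conditional odds ratio and a Cox model a hazard ratio. At stake are some power and a single, clearly designated answer on 90-day mortality.

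**Working it through.** **1. Reproduce the planned sample size.** Inputs from the Sample size section: p1 = 0.25, p2 = 0.25 − 0.08 = 0.17, power 80%, alpha 0.05 (two-sided, per the Statistical and analytical plan). The mean proportion is 0.21.

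- A = √(2 × 0.21 × 0.79) = 0.5760
- B = √(0.25 × 0.75 + 0.17 × 0.83) = 0.5732
- Uncorrected n = (1.960 × A + 0.842 × B)² / 0.08² = 405.7, so 406 per group
- With continuity correction, n = (405.7/4) × [1 + √(1 + 4/(405.7 × 0.08))]² = 430.4, so 431 per group

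This matches the stated 431 exactly. The trial is sized for an unadjusted comparison of two proportions.

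**2. Power of the named test.** For the uncorrected chi-square at 431 per group, z = (√431 × 0.08 − 1.960 × 0.5760)/0.5732 = 0.928, which gives power of 82.3%.

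**3. What center and severity would add.** Simulated trials of 862 patients, center-stratified blocks of four, 25% versus 17% mortality, 2,000 trials per scenario. Three tests were compared: plain chi-square, Cochran-Mantel-Haenszel (CMH) stratified by center, and logistic regression on treatment, center and a severity score.

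Assumptions not in the article: five centers with shares of 60/10/10/10/10%; center log-odds offsets of 0, ±0.3 or ±0.7; a standardized severity score with log-odds slope 0, 0.6, 0.9 or 1.2 per SD. The AUC below is for center and score together.

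| Slope | Center offset | AUC | Chi-square | CMH by center | Logistic, center + score |
|---|---|---|---|---|---|
| 0 | 0 | 0.50 | 81.7% | 81.6% | 81.8% |
| 0 | ±0.3 | 0.55 | 81.3% | 81.7% | 82.0% |
| 0 | ±0.7 | 0.61 | 81.8% | 82.9% | 82.8% |
| 0.6 | 0 | 0.66 | 83.8% | 83.7% | 85.4% |
| 0.6 | ±0.3 | 0.67 | 84.3% | 84.6% | 87.0% |
| 0.6 | ±0.7 | 0.69 | 83.2% | 83.7% | 85.4% |
| 0.9 | 0 | 0.72 | 82.4% | 82.3% | 86.8% |
| 0.9 | ±0.3 | 0.73 | 82.6% | 82.6% | 87.1% |
| 0.9 | ±0.7 | 0.74 | 84.2% | 84.9% | 89.6% |
| 1.2 | 0 | 0.78 | 83.2% | 83.0% | 89.2% |
| 1.2 | ±0.3 | 0.78 | 82.8% | 82.9% | 90.0% |
| 1.2 | ±0.7 | 0.79 | 82.0% | 82.8% | 89.8% |

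The Monte Carlo standard error of each power is about √(0.83 × 0.17/2000) = 0.8 points. The three tests were applied to the same simulated trials.

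- Center alone (CMH minus chi-square): −0.2 to +1.1 points.
- Center plus score (logistic minus chi-square): 1.6 to 2.7 points at slope 0.6, 4.4 to 5.4 at slope 0.9, and 6.0 to 7.8 at slope 1.2.

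**4. The same gain in patients.** Required size is proportional to (1.960 + z of the power)². The smallest gain, 83.8% to 85.4%, gives 9.08/8.68 = 1.05. The largest, 82.0% to 89.8%, gives 10.43/8.27 = 1.26. Adjustment is therefore worth about 5% to 26% more patients over these assumptions.

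**5. Validity.** With no treatment effect, the chi-square rejected in 3.7% to 5.5% of trials (standard error about 0.5 points), CMH in 4.2% to 5.6%, and the logistic model in 4.1% to 5.3%. The plain test does not inflate the type I error.

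**The case against.** The strongest reply is that nothing here is wrong. An unadjusted chi-square is a valid primary test, the sample size was computed for it, and it exceeds the planned 80% power. An article may also leave covariate lists to the full protocol or analysis plan. All of that stands, and the missing list is not a fault in itself. What remains is that the article does name a primary test, that test uses neither center nor APACHE II, and its relation to the adjusted models is left open.

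A reader might infer four stronger things, none of which the article supports:

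- **That ignoring center makes the test materially too conservative.** The direction is right in principle, but the effect was 0 to 1 point of power. A center-stratified CMH test alone would recover almost nothing; nearly all the gain comes from the severity score.
- **That the information is thrown away.** Adjusted logistic and Cox analyses are planned, and APACHE II defines a subgroup. The information is unused in the named test, not in the whole plan.
- **That covariates will be chosen after seeing interim results.** The Discussion and Trial status section says that the biostatistician was not blinded to the March 2012 interim results. No section says when covariates are chosen or by whom.
- **That a particular gain is assured.** The article gives no figure for how well APACHE II predicts 90-day death.

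**Conclusion.** The point holds as one of efficiency and of a clearly designated primary analysis. The chi-square is sound and delivers about 82% power at 431 per group. Under the assumed center shares and offsets, center alone is worth about 0 to 1 point. Center plus severity is worth roughly 2 to 8 points for an AUC of about 0.67 to 0.78, and that range is an assumption. If APACHE II predicted 90-day death weakly in this population, the gain would fall toward zero. The change is worth making because the data are already collected, but the trial would not be invalid without it.

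**What to change.** Name one primary analysis of 90-day mortality: a regression with treatment, center and continuous APACHE II as fixed, listed covariates. Report the standardized (marginal) risk difference and risk ratio with 95% CIs, so that the absolute risk reduction and number needed to treat come from the same analysis as the test. Keep the plain chi-square as a sensitivity analysis. For the primary outcome, delete the qualifier that makes covariate control conditional, and label the Cox and other survival analyses as supportive.

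The first interim analysis, on 287 patients, has been done, and the next is due at two-thirds of recruitment. The change should therefore be written, dated and approved before that look by people who have not seen unblinded results.

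It needs no new data and no more patients. The costs are a documented change of primary test during the trial, which must be explained openly, and a rule fixed in the same amendment for pooling centers that recruit too few patients.

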[12]. An RCT with 200 mechanically ventilated patients and a second RCT with 1,000 patients with acute lung injury showed that a strategy of initial trophic enteral feeding (10 mL/hour) compared with standard targeted enteral feeding goals for up to six days reduced gastrointestinal tolerance, but did not improve ventilator-free days or 60-day mortality
[13,14]. The intervention arms of these two RCTs instituted very low trophic feeding in critically ill patients with acute lung injury. In contrast, an RCT of 240 general medical-surgical mechanically ventilated patients conducted by our investigative team compared the efficacy of a moderate hypo caloric (60% to 70% of calculated caloric requirement) versus a eucaloric (90% to 100%) diet
[15]. The endpoints of ICU, 28-day and 90-day mortality were not statistically different (17.5%, versus 21.7%, *P* = 0.42; 18.3% versus 23.3%, *P* = 0.34 and 31.0% versus 39.3%, *P* = 0.19, respectively)
[15]. However, hospital mortality was reduced in the hypo caloric diet group (30% versus 42.5%, *P* = 0.04), and there was a trend towards shorter ICU LOS
[15]. In contrast to very low caloric or trophic enteral feeding, it remains unclear whether a moderate caloric intake may improve survival and reduce morbidity.

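### The rule that adjusted relative risks come from Cox regression is not limited to fixed-horizon mortality; for ICU and hospital mortality a Cox estimate is not a sound relative risk

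*Protocol article*

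**What the plan says.** Under Outcome measures the article lists the secondary mortality endpoints: "Secondary outcomes include ICU, hospital, 28-day and 180-day mortality rates". It adds one time limit: "Hospital mortality is censored at one year from the date of enrollment". It gives no rule for patients discharged alive.

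Statistical and analytical plan then sets out, in this order:

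- the main comparison: "The primary and secondary outcomes between the two intervention groups will be compared using the Chi-square test";
- logistic regression to test the intervention effect on binary outcomes when covariates are controlled;
- the adjusted effect measure: "Adjusted relative risks and associated 95% CIs will be estimated using Cox proportional hazards regression modeling";
- survival analysis as a further analysis of the primary outcome.

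The Cox sentence names no outcome, time scale or censoring rule. It comes straight after the sentence on binary outcomes. The sentence after it adds survival analysis for the primary outcome as something extra, so the Cox sentence reads as a wider provision than the primary outcome alone.

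**The concern.** Death in the ICU or in hospital can no longer occur once a patient has left alive. Discharge alive is therefore a competing event, not loss to follow-up. A Cox model that censors at discharge compares deaths per day spent in the unit. A relative risk compares the proportions who die there. The two differ whenever the arms differ in length of stay.

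A stay difference is a real possibility in this trial. ICU and hospital stay are outcomes compared between arms, and on the team's earlier trial the Background reports that "there was a trend towards shorter ICU LOS". Hospital mortality will also be read closely. It was the one mortality endpoint on which that earlier trial was significant (30% versus 42.5%), and the Sample size section cites it when introducing the 8-point effect. The chi-square comparison and the adjusted relative risk could then tell different stories about the same deaths, with nothing in the article to explain why.

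**Working it through.** **The plan's own figure.** The inputs are under Sample size ("Based on an estimated 90-day mortality of 25% and using a power of 80% and an alpha of 0.05", 8-point decrease, 431 per group) and Statistical and analytical plan ("All tests of significance will be at the 5% significance level, and two-sided").

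- Without continuity correction: n = [1.96·√(2·0.21·0.79) + 0.842·√(0.25·0.75 + 0.17·0.83)]² / 0.08² = 405.7, so 406.
- With correction: (405.7/4)·[1 + √(1 + 4/(405.7·0.08))]² = 430.4, so 431.

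The stated figure is reproduced. Nothing below changes it.

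**Model for the check (assumption).** Constant hazards, with p the risk of dying in hospital and L the mean stay. The death hazard is p/L and the discharge hazard is (1 − p)/L. Let r be the stay ratio, underfeeding over target. If discharge alive is censored, Cox estimates

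HR = (p_U/L_U)/(p_T/L_T) = RR / r.

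The values 0.9 and 0.8 for r are assumptions. The value 0.73 is 16.7/22.9 days, from the trial of early aggressive versus late feeding cited in the Background, which made a different comparison.

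| Case | True RR | HR at r = 0.9 | r = 0.8 | r = 0.73 |
|---|---|---|---|---|
| A. Equal death risk | 1.00 | 1.11 | 1.25 | 1.37 |
| B. Equal daily death hazard, faster discharge | 0.90, 0.80, 0.73 | 1.00 | 1.00 | 1.00 |
| C. Earlier trial's risks, 30% v 42.5% | 0.71 | 0.78 | 0.88 | 0.97 |

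If the target arm leaves sooner, r exceeds 1 and each distortion reverses.

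**Size against sampling error.** Take 431 per arm and, as an assumption, 25% hospital mortality in each. Deaths per arm are 431·0.25 = 107.75, and the SE of the log HR is √(2/107.75) = 0.136. In case A the shift is ln(1.11)/0.136 = 0.77 SE, ln(1.25)/0.136 = 1.6 SE and ln(1.37)/0.136 = 2.3 SE.

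**Discharged patients kept at risk to one year.** This is the other reading of the one-year limit. Under proportional hazards, 30% v 42.5% gives HR = ln(0.70)/ln(0.575) = 0.357/0.553 = 0.64. Cox fits to simulated exponential stays of equal length gave 0.65. The risk ratio is 0.71, so the hazard ratio lies further from 1.

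**One common time for every patient.** With Breslow ties the point estimate is the risk ratio exactly (1.062 against 1.062 in one simulated data set, where censoring at discharge gave 1.29). The model-based SE is too large, however. At 25% in both arms it is √(2/107.75) = 0.136, against a binomial SE of the log risk ratio of √(2·0.75/107.75) = 0.118. At RR = 1 the 95% interval is 0.77 to 1.31 instead of 0.79 to 1.26. A robust variance is needed to correct this.

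**The case against.** The strongest reply is that the article never assigns ICU or hospital mortality to Cox regression. It calls them rates, compares them by chi-square and tests binary outcomes by logistic regression, and only the primary outcome is named for survival analysis. A condensed article may also leave the handling of discharge to a fuller plan. Part of this stands: coverage of these two endpoints is a reading, not an explicit assignment, and a missing discharge rule alone would be no finding. What remains is a stated, unrestricted choice of Cox regression for adjusted relative risks, and that choice suits these endpoints poorly.

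Three stronger inferences are tempting and are not supported:

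- *Discharge alive can only be censored.* It need not be. Patients can be kept at risk to one year or given a common time, and the article does not say which.
- *Underfeeding would look like excess death.* This needs censoring at discharge and a stay that shortens proportionally more than the death risk. In cases B and C the hazard ratio does not exceed 1; a benefit is hidden or diluted instead.
- *The direction is known.* The Background cites shorter stay with lower intake, but also a cluster-randomized trial in which the arm given more calories had a significantly shorter hospital stay. The team's own result was only a trend, and in ICU stay.

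**Conclusion.** The point holds as a defect in the adjusted effect estimate for two secondary endpoints. As worded, the Cox sentence can be applied to ICU and hospital mortality, and none of the three ordinary set-ups yields a sound adjusted relative risk with a correct interval by default. Under censoring at discharge, a 10% to 27% difference in stay moves the estimate by about 0.8 to 2.3 standard errors at equal risk. These sizes rest on constant hazards, on assumed or borrowed stay ratios and on an assumed 25% hospital mortality. They illustrate the mechanism and do not predict this trial's result.

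The chi-square and logistic tests of ICU and hospital mortality do not depend on time to discharge. Mortality at 28, 90 and 180 days is also free of the problem, because discharge does not end follow-up for it. The primary comparison and the sample size stand.

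**What to change.** In Statistical and analytical plan:

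1. Limit Cox regression and Kaplan-Meier curves to all-cause mortality over a fixed horizon (28, 90 and 180 days), and report the Cox estimate as a hazard ratio.
2. Estimate adjusted risk ratios for ICU and hospital mortality with a log-binomial model, a modified Poisson model with robust variance, or standardization of the logistic model already planned. Count patients discharged alive, or still in hospital at one year, as non-events.
3. If a time course is shown for these endpoints, use cumulative incidence with discharge alive as the competing event.

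The cost is a few sentences of wording. The data are already collected, the sample size is unchanged and the planned software can do it. The small downside is that time to death within the unit is not used. By the article's account, recruitment is still active and the investigators, apart from the biostatistician, remain blinded to the interim results, so the change can be made before final results are known.
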